## Abstract

*Background. *Dysphagia is one of the most common complications of stroke. Acupuncture is widely employed to treat poststroke dysphagia in East Asia. No evidence is established to support such treatment approach. This proposed study aims to evaluate the effectiveness and safety of acupuncture for the treatment of poststroke dysphagia.* Methods and Design.* This is a multicenter, pragmatic, single-blinded, nonrandomized controlled clinical trial. A total of 140 eligible patients will be enrolled in the study. Subjects who are eligible in study but refuse to have acupuncture treatment will be put on the no-acupuncture control arm. Both groups of patients will receive standard routine care, while the patients of intervention group will receive add-on standardized acupuncture treatment. Each participant in intervention group will receive a total of 24 sessions of acupuncture treatment (three times per week). The primary outcome measure is the Royal Brisbane Hospital Outcome Measure for Swallowing (RBHOMS). Secondary outcome measures include functional oral intake scale, swallow quality-of-life questionnaire in Chinese version, BMI of the participant, and adverse events. All outcome measures will be assessed at baseline, at the end of acupuncture treatment (month 2), and at two months after treatment (month 4).* Ethics and Dissemination.* The ethics approval of clinical research study was granted by the Research Ethics Committee of both New Territories East and West Cluster of Hong Kong. Written informed consent will be obtained from all participants and the study will be undertaken according to the ICH-GCP Guidelines.* Trial Registration.* This trial is registered with chictr.org (registration number: ChiCTR-TRC-12002621 and registration date: 2012-10-26).

## 1. Background

Dysphagia, sometimes as part of pseudobulbar palsy, is one of the most common complications of stroke among patients. The prevalence of poststroke dysphagia ranges widely from 29% to 81% due to various methods of diagnosis, time after stroke, and the types of lesions [1–3]. Dysphagia may naturally resolve in many patients over the first 7 days after the cerebrovascular event and about 10% of them may develop swallowing problems six months after stroke [4, 5]. Dysphagia is known to be associated with an increased risk of pneumonia, malnutrition, disability, and mortality [2, 6, 7]. Many dysphagia management options are available today, including texture-modified diets, swallowing therapy programmes, nonoral feeding, medications, and physical stimulation. However, clinical evidence to establish their roles in the management of poststroke dysphagia is limited [8, 9].

Acupuncture is widely employed in management of poststroke complication in Asia and Pacific region. According to a report which was published by World Health Organization (WHO) in 2003, stroke is one of indications of acupuncture (Chmielnicki, 2014) [10]. Moreover, some clinical trials have been conducted to evaluate the effectiveness and safety of acupuncture for poststroke dysphagia. A study conducted by Ding et al. 1996 compared the acupuncture group and conventional western medication treatment. It demonstrated that the average recovery time of acupuncture group is shorter than conventional western medication group [11].

A systematic review which included about 35 randomized controlled trials of acupuncture for dysphagia has shown that acupuncture may improve swallowing function [12]. Some mechanistic studies had also illustrated that acupuncture is able to regulate the cortex and the swallowing center of the reticular structure of the brain stem to control swallowing reflection and coordinate motor movement of the swallow-related muscles, as well as directly improving the recovery of the injured peripheral nerves [13, 14]. Other studies had also found that acupuncture treatment could attenuate the plasma endothelin and nitric oxide (NO) level, regulate the imbalance between prostacyclin and thromboxane A2, and improve blood viscosity, thereby collectively contributing to the therapeutic effect for poststroke dysphagia [15–17].

Nevertheless, several limitations of these studies may potentially bias the result and render the findings inconclusive. Xie et al. had undertaken a systematic review which was published in Cochrane Library [18], demonstrating that there is no enough evidence to make any conclusion about treatment effect of poststroke dysphagia. Some flaws in methodology existed in the previous study to hinder the conclusive finding, such as small sample size and lack of blinding in assessment [19]. In addition, most previous studies are open-labelled trials. Blinding was usually not applied to the outcome assessors. The lack of blinding would seriously weaken the credibility of the study. Therefore, a high quality and well-designed randomized controlled trial is urgently required.

The previous studies, together with our previous experience, suggest that there is a need to conduct a well-designed pilot study for assessing the effectiveness and safety of acupuncture for poststroke dysphagia. The early conclusion of this pilot study is able to provide evidence for conducting a full-scale rigorously designed clinical trial in future.

## 2. Objective

This study is to evaluate the effectiveness and safety of acupuncture for the treatment of dysphagia as a complication of stroke.

## 3. Methods and Design

### 3.1. Study Design

This is a multicenter, pragmatic clinical trial comparing real acupuncture intervention with no acupuncture to evaluate the treatment effects of acupuncture on the outpatient population of poststroke dysphagia. Owing to the characteristic of poststroke dysphagia patient and the nature of acupuncture, it is not feasible to implement the sham acupuncture in this study. The patients in acupuncture group and no-acupuncture control group will be in 1 : 1 allocation ratio. Subjects who are eligible in study and willing to accept acupuncture will be allocated to intervention group, while subjects eligible in study but refuse to have acupuncture treatment will be put on the no-acupuncture control arm. In the real acupuncture group, patients will receive acupuncture intervention in addition to conventional treatment. Real acupuncture group is defined as the group in the study that receives a series of sessions of acupuncture treatment which is being tested. The study will be conducted in several Chinese medicine clinics including The Pok Oi Hospital, The Chinese University of Hong Kong Clinical Center for Teaching and Research in Chinese Medicine (Shatin and Yuen Long), and The Yan Oi Tong, The Chinese University of Hong Kong Clinical Center for Teaching and Research in Chinese Medicine (Tuen Mun). Acupuncture treatment may also be conducted at the affiliated mobile clinics of these centers. This project is approved by both the Joint Chinese University of Hong Kong-New Territories East Cluster Clinical Research Ethics Committee (CRE-2012.236-T) and New Territories West Cluster Clinical Research Ethics Committee (NTWC/CREC/1281/14). Written informed consent is obtained from each participant. The study will be conducted according to ICH-GCP Guidelines. The study design is described in Figure 1.

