## 5. Intervention

Patients in both acupuncture and no-acupuncture control group will receive the conventional supportive and rehabilitative treatment, such as swallowing therapy programmes, nonoral feeding, medications, and physical stimulation [8, 9]. On top of the supportive treatment, patients in the acupuncture group will receive real acupuncture treatment, while patients assigned to the control group will receive no-acupuncture treatment during the study. Baseline assessment will be conducted for all eligible participants. The participants who agree to accept acupuncture treatment will be allocated to treatment group, while those who refuse to accept acupuncture treatment will be allocated to control arm.

All acupuncture treatment sessions will be performed by two to three acupuncturists who are registered Chinese Medicine Practitioners in Hong Kong and have at least 3 years of clinical experience in acupuncture practice. Interventions will be conducted according to STRICTA and ICH-GCP guidelines. To ensure the consistency of skill of various acupuncturists, two to three training workshops will be provided to acupuncturists who have participated in the study prior to the commerce of the study. The acupuncture experts panel of School of Chinese Medicine, The Chinese University of Hong Kong, will provide technique training on the selection of acupuncture points and needling techniques. The workshops will be videotaped for education purpose.

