## 10. Sample Size Estimation

The primary outcome measure is Royal Brisbane Hospital Outcome Measure for Swallowing (RBHOMS), which is a 10-point ordinal scale that ranges over four stages of oral intake from stage “A” (nil by mouth) to “D” (maintaining oral intake). The sample size is estimated to compare the proportion of those who are rated at stage “D.” Based on our previous clinical study [23], we estimate that 60 participants in each group will be needed to detect 20% difference of the proportion between the treatment and control group with a false positive error of 5% and power of 80%. To compensate for dropouts during treatment period, we inflate this value by 15% and hence a total of 140 patients will be recruited, with 70 each in the treatment and control group.

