Blinding is a crucial measure to assure the quality of the trial. All outcome assessor and statistician will be kept blind throughout the whole process. We will minimize the interaction between the patients and outcome assessors. Neither the RBHOMS assessor nor the staff who administer the questionnaire knows the group allocation of the participants.

One main limitation of this study is lack of randomization. Randomization is a key procedure to minimize the selection bias and ensure the comparability of all parameters between the intervention group and control group. However, concerning the timeframe and budget of our pilot study, nonrandomization approach will be utilized. To reduce the selection bias of our study, subjects will be recruited from different sources, including hospitals, speech therapy outpatient clinics, and Chinese medicine clinics. Moreover, all the prognostic factors and baseline characteristics of participants such as gender, age, occupation, life style, and onset time of stroke will be controlled in both acupuncture group and nonacupuncture control group. All data will be collected to examine the baseline comparability and explore the possible sources of dissimilarity and make proper statistical adjustment later.

As for all clinical trials, subject recruitment is one of the most critical factors for the trial's successful implementation. In our study, various venues and approaches will be utilized to augment the subject recruitment process. Free Chinese medicine consultation will be provided to control arm participants as an incentive. In addition, we will also hold promotional talks in the Chinese medicine clinics to facilitate the recruitment process. Moreover, we may also place advertisements on local newspapers and contact the stroke patients association to boost subject recruitment if recruitments from hospitals and Chinese medicine clinics turn out to be undesirable.

Nonetheless, most of potential subjects of this study are stroke sufferers. They always have other complications, such as immobility. In order to reduce the dropout rate and to enhance the compliance of patients, some treatment sessions may be conducted at affiliated mobile clinics.

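### A 1:1 ratio with 70 per arm is stated, but patients choose their own arm, so the 80% power holds only if the arms happen to be, or are made, equal

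*Protocol article*

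**What the plan says.** Section 3.1 gives the ratio as a feature of the design: "The patients in acupuncture group and no-acupuncture control group will be in 1 : 1 allocation ratio". The next sentence gives the assignment rule: "Subjects who are eligible in study and willing to accept acupuncture will be allocated to intervention group", whereas "subjects eligible in study but refuse to have acupuncture treatment will be put on the no-acupuncture control arm". Section 5 repeats it: "those who refuse to accept acupuncture treatment will be allocated to control arm".

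Section 10 sizes the trial on equal arms. It says that "60 participants in each group will be needed to detect 20% difference of the proportion between the treatment and control group", with a 5% false positive error and 80% power. After a 15% inflation for dropout, "a total of 140 patients will be recruited, with 70 each in the treatment and control group".

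The Discussion (section 12) names the lack of randomisation as a main limitation and promises a baseline comparison and later adjustment. The text does not say how equal arms would be reached: there is no cap, quota, matching or closing rule. Section 3.1 refers to Figure 1 for the design, and that figure was not available for this review.

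**The concern.** When patients choose their arm, the split equals the share who accept, and the trial does not set that share. The document therefore claims equal arms, on which its sample size rests, under a rule that does not produce them. It can be followed in two ways, and each has a cost.

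- **Stop at 140, whatever the split.** The arms may be unequal, and the power then differs from the stated 80%.
- **Fill each arm to 70.** Unless acceptance is close to one half, one arm fills first. If it closes, the remainder of the other arm is recruited with no concurrent comparators. Group and calendar period are then inseparable for those patients, and adjustment for baseline characteristics cannot repair that.

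Both are separate from the self-selection that the Discussion already admits.

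**Working it through.** **Inputs from the documents.** Sections 3.1 and 10: 1:1 ratio, 60 per arm analysed, a 20-point difference in the proportion at stage D, alpha 0.05, power 80%, 15% inflation, 70 per arm, 140 in total. Section 11: chi-square test, two-sided.

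**Assumed, because the documents do not give them.** The control proportion at stage D, and the share of eligible patients who accept acupuncture.

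**1. The plan's own figures.**
- From 60 to 70 per arm: 60 × 1.15 = 69 and 60 / 0.85 = 70.6, so 70 per arm and 140 in total are consistent with the stated inflation.
- 60 per arm for 80% power: the usual two-proportion formula gives 60 at 9% v 29% and at 71% v 91%, and 62 at 10% v 30% and at 70% v 90%. The figure is reproduced, but only if the control rate is near one of these ends. The arithmetic is not at fault; equal arms are assumed throughout.

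**2. Chance of equal arms if enrolment stops at 140.** With acceptance share q, P(70/70) = C(140,70) × q^70 × (1 − q)^70.
- q = 50%: 6.7% for exactly 70/70, and 55% for 66 to 74 in the acupuncture arm.
- q = 60%: 0.4% and 5%.
- q = two thirds: about 0 and 0.05%.

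The results are the same if refusal is the commoner choice.

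**3. Power at unequal splits, 120 analysed.** Method: sum the binomial probabilities of all outcomes (x of n1, y of n2) for which the uncorrected two-sided chi-square test rejects at 0.05. The acupuncture proportion is taken as the control proportion plus 20 points.

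| Acupuncture:control | 10% v 30% | 70% v 90% |
|---|---|---|
| 60:60 | 80.2% | 80.2% |
| 72:48 | 78.8% | 81.9% |
| 80:40 | 73.2% | 77.5% |
| 90:30 | 64.1% | 72.6% |
| 40:80 | 77.5% | 73.2% |
| 30:90 | 72.6% | 64.1% |

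The control rate is given first in each column heading. The last two rows mirror the two above them, because exchanging the arms and counting failures instead of successes turns one scenario into the other. A 60:40 split costs little or nothing here. A 2:1 split costs 2.7 to 7.0 points and a 3:1 split 7.6 to 16.1 points, depending on the direction and the control rate.

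**4. If each arm is capped at 70.** Let m be the share making the commoner choice. The fuller arm closes after about 70/m eligible patients.
- m = 50%: 140 eligible patients; both arms fill at about the same time.
- m = 60%: 70/0.60 = 117 eligible patients. The other arm then holds 117 − 70 = 47, so about 23 of its 70 come later. Reaching 70 there takes 70/0.40 = 175 eligible patients, of whom 175 − 140 = 35 are turned away.
- m = two thirds: 105 eligible patients. The other arm holds 35, so 35 of its 70 come later. Reaching 70 takes 210 eligible patients, of whom 70 are turned away.

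**The case against.** The sponsor could say that 70 per arm reads naturally as a recruitment target, that quotas and screening logs belong in the full protocol rather than a condensed article, and that the Discussion is open about the lack of randomisation. Some of this stands: the absence of an enrolment manual would be no finding. But section 3.1 goes beyond a target. It states an allocation ratio and, in the next sentence, a rule that does not yield it. The admitted limitation concerns comparability of the arms, not how they become equal in size.

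A reader might infer more, and the documents do not support these stronger readings:

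- **That equal arms require staff to select patients case by case, knowing each one's arm.** A fixed cap with consecutive enrolment would reach 70/70 without such judgement, and near 50% acceptance rough balance can arise by chance. Nothing says that entry will be steered by prognosis.
- **That the acupuncture arm will fill first.** Some recruitment is at Chinese medicine clinics, and "we will also hold promotional talks in the Chinese medicine clinics to facilitate the recruitment process". But the same section offers a free consultation to control patients only. Section 3.2 describes referral by hospital speech therapists, and 24 sessions at three a week are a plausible reason to refuse. The direction is unknown.
- **That power necessarily drops a great deal.** Moderate imbalance hardly matters. Under a mid-range control rate power is low even with equal arms (68.4% at 20% v 40% with 60:60); that shortfall comes from the unstated control rate and should not be charged to imbalance.

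**Conclusion.** The point holds as an inconsistency with a conditional cost. The protocol states 1:1 and 70 per arm, while its assignment rule leaves the split to patient choice. The 80% power is therefore conditional on equality that the design does not secure. Under control rates consistent with 60 per arm, the loss is negligible at 60:40, up to about 7 points at 2:1 and up to about 16 at 3:1. Enforcing 70/70 by caps would restore the sizing but could leave part of one arm without concurrent comparators: about a third of it at 60:40 and half at 2:1.

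This rests on assumed acceptance shares, assumed control rates, and 120 patients analysed. Which arm would be short is not known, and Figure 1, not seen here, could describe a mechanism.

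**What to change.** - **Section 3.1:** delete the 1:1 ratio. Say that arm sizes follow patient choice and that 70 per arm is a recruitment target.
- **Enrolment rule:** screen consecutive patients at each recruiting clinic, and record eligibility and baseline RBHOMS before asking about acupuncture preference. Keep both arms open over the same clinics and calendar periods rather than filling one after the other.
- **Section 10:** beside the 80%, state the power at 2:1 and 3:1 splits in either direction, with the control rate assumed.

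Strict balancing of accepters and refusers within every clinic is not recommended as a default, because it too turns patients away by their known choice.

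The cost is protocol wording and a screening log. The stated power becomes less favourable, and recruitment may be slower or the final arms unequal.

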### 3.2. Subject Recruitment

The patients may be recruited from The Pok Oi Hospital, The Chinese University of Hong Kong Clinical Center for Teaching and Research in Chinese Medicine (Shatin and Yuen Long), and The Yan Oi Tong, The Chinese University of Hong Kong Clinical Center for Teaching and Research in Chinese Medicine (Tuen Mun), as well as speech therapy clinics at Prince of Wales Hospital, Shatin Hospital, and Tuen Mun Hospital. The suitable poststroke dysphagia patients will be referred to by the speech therapists of the Speech Therapy Department from above hospitals. The Research Assistant will go to each of speech therapy outpatient clinics of all above three hospitals once or twice a week to explain to those potentially suitable patients (or their relatives/caretakers) the details of the research. All potential participants will be informed of the study such as objective, scope, procedure, and potential benefit and risks of the trial. A paper-formed voluntarily signed written inform consent will be obtained from participants. Under some circumstances, oral informed consent is acceptable, for instance, if participants cannot read. One hundred and forty eligible participants will be recruited from above sites according to the inclusion and exclusion criteria.

### 3.3. Inclusion Criteria

Age between 30–90 years oldWith an ischemic or haemorrhagic stroke confirmed by a CT scanWithin 12 months after the first-time stroke (ischemic or haemorrhagic)On modified diet due to dysphagia fulfilling RBHOMS with 2–8 pointsAble to give informed consent (by patient himself/herself or by caretaker)

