## 8. Primary Outcome

Royal Brisbane Hospital Outcome Measure for Swallowing (RBHOMS) is a valid bedside scale for monitoring difficulties in daily swallowing function based on clinical indicators of swallowing, but not on texture-modified diets [20]. RBHOMS is a 10-point ordinal scale that ranges over four stages of oral intake: stage A, nil by mouth (levels 1–3); stage B, commencing oral intake (level 4); stage C, establishing oral intake (levels 5–7), and stage D, maintaining oral (levels 8–10). Both acupuncture group and nonacupuncture control group patient will be conducted three times RBHOMS, with one being conducted at baseline, one at the end of treatment (2 months after inclusion), and the last one at the end of follow-up period (2 months after treatment completion). All RBHOMS will be conducted by a registered speech therapist blinded to group allocation.

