## 11. Data Analysis

All analyses will be conducted according to the intention-to-treat principle. Descriptive statistics will be computed for each of the analyzed variables. For the primary outcome, chi square test will be used. All continuous variables such as swallowing time, swallow quality-of-life, and BMI will be analyzed using *t*-test where appropriate. Swallow function scores will be analyzed using Mann–Whitney *U* test. The possible relationship between some baseline data and main outcomes will be explored using multivariable analysis. All statistical tests will be two-sided, and *p* < 0.05 is considered statistically significant. The statistical software of SPSS (SPSS, SPSS Inc., Chicago, USA) version 20 will be used for the analysis.

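### Entry at RBHOMS 2–8 overlaps the stage D success range (levels 8–10), so level 8 patients can enter already counted as successes

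*Protocol article*

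**What the plan says.** Three statements in the protocol article bear on this.

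- Section 3.3 (Inclusion Criteria) admits patients "On modified diet due to dysphagia fulfilling RBHOMS with 2–8" points.
- Section 8 (Primary Outcome) divides the scale into four stages, the last being "stage D, maintaining oral (levels 8–10").
- Section 10 (Sample Size Estimation): "The sample size is estimated to compare the proportion of those who are rated at stage" D. Its figure is "60 participants in each group will be needed to detect 20% difference of the proportion between the treatment and control group". The type I error rate behind this is set at 5% and the power at 80%.

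Section 11 (Data Analysis) adds: "For the primary outcome, chi square test will be used". It does not name the categories to be tabulated. Nowhere does the article restrict the comparison to patients below stage D at entry, or define success as a change from baseline.

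**The concern.** Level 8 is both an allowed entry level and a success on the only primary comparison that the protocol names. A patient who enters at 8 cannot show benefit on that endpoint: no change is scored as success, and a true gain to 9 or 10 scores the same. Such a patient can affect the comparison only by deteriorating, or by adding a success to whichever arm he or she has chosen.

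Two things are at stake. First, patients who count as successes in both arms whatever happens shrink the difference between the arms. Second, the arms are formed by willingness to have acupuncture, so nothing in the design balances the level 8 shares, and an imbalance passes directly into the primary result.

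**Working it through.** **The overlap.** Entry levels are {2, 3, 4, 5, 6, 7, 8} (section 3.3). Stage D is {8, 9, 10} (section 8). The common element is 8. This needs no calculation.

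**The plan's own figure.** Inputs from sections 10 and 11: a 20-point difference, two-sided 5%, 80% power, 60 per group. No control rate is stated, so the figure can be neither confirmed nor refuted outright. The usual pooled-variance formula without continuity correction gives:

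- 9% vs 29%: 60 per group
- 10% vs 30%, or 70% vs 90%: 62 per group
- 40% vs 60%: 97 per group (60 per group would then give 59% power)

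So about 60 per group fits a pair of rates near either end of the scale. I carry both 10% vs 30% and 70% vs 90% forward.

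**Power formula.** With n per group, d = p2 − p1 and p̄ the mean of the two rates:

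power = Φ{ [d − 1.96·√(2p̄(1 − p̄)/n)] / √[(p1(1 − p1) + p2(1 − p2))/n] }

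For 10% vs 30% and n = 60: √(0.32/60) = 0.0730 and √(0.30/60) = 0.0707, so (0.20 − 0.1431)/0.0707 = 0.804 and power is 78.9%. By symmetry 70% vs 90% also gives 78.9%.

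**Dilution.** Assume that a share f of each arm enters at level 8 and stays in stage D, and that the other patients reach stage D at rate p. The arm rate becomes f + (1 − f)p, and the difference becomes (1 − f) × 20 points whatever the control rate. The values of f are assumptions; 1/7 is what seven equally common entry levels would give.

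| f | Difference (points) | Rates from 10% vs 30% | Power, n = 60 | Rates from 70% vs 90% | Power, n = 60 |
|---|---|---|---|---|---|
| 0 | 20 | 10.0% vs 30.0% | 79% | 70.0% vs 90.0% | 79% |
| 10% | 18 | 19.0% vs 37.0% | 60% | 73.0% vs 91.0% | 73% |
| 1/7 | 17 | 22.9% vs 40.0% | 53% | 74.3% vs 91.4% | 71% |
| 20% | 16 | 28.0% vs 44.0% | 45% | 76.0% vs 92.0% | 67% |

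**Imbalance with no treatment effect.** Suppose 20% of one arm and 10% of the other enter at level 8 and stay in stage D, and 20% of the remaining patients reach stage D in both arms. Then (0.20 + 0.80 × 0.20) − (0.10 + 0.90 × 0.20) = 0.36 − 0.28 = 8 points, which is 40% of the 20-point target.

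**Analysing only baseline 2–7.** If 60 per arm are available, 60(1 − f) is about 54, 51 or 48 per arm. The full 20-point difference is kept, and power is about 75%, 72% or 69% at either pair of rates. This exceeds the corresponding diluted figure in every row of the table: by a wide margin at 10% vs 30%, and by only 1 to 2 points at 70% vs 90%.

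**The case against.** The overlap itself is not in dispute, but several stronger readings are tempting and the document does not support them.

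- **That some participants will certainly meet the endpoint at baseline.** The protocol permits level 8 entrants; it does not say how many there will be.
- **That stage D is fixed beyond doubt as the primary endpoint.** Section 8 presents an ordinal scale, and stage D as the compared quantity appears only in section 10. Still, it is the only primary comparison named, and a chi-square test suits it; the ordinal swallow function score is given a Mann–Whitney test instead. If stage D is not the endpoint, the sample size refers to something that is not going to be tested.
- **That level 8 entrants can only dilute the contrast.** With unequal shares they can also inflate or reverse it, and a level 8 patient who deteriorates does contribute information.
- **That power necessarily drops to around half.** This holds for 10% vs 30%. From 70% vs 90%, which fits the stated sample size equally well, the loss is modest.
- **That the 20 points must apply to patients below stage D.** Section 10 states the difference between whole groups, from an earlier study that is not shown. If that study's population already included level 8 patients, the dilution above would be counted twice.

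It can also be said that imbalance is simply the general problem of patient-chosen arms, which section 12 (Discussion) admits and proposes to address by later adjustment. In part this is right: an excess of level 7 over level 2 patients would also shift the stage D proportion under entry at 2–7. But the examples of prognostic factors in section 12 do not include baseline RBHOMS, the multivariable analysis in section 11 is exploratory, and adjustment cannot give a patient already in stage D a transition into it.

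Nor does the modified-diet condition remove the overlap: the criterion itself lists level 8 as compatible with it.

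**Conclusion.** The point holds. Sections 3.3, 8 and 10 cannot all stand as written if the primary comparison is to show what treatment did, because an eligible level 8 patient is a success before treatment starts.

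The size is conditional. It rests on an assumed level 8 share of 10% to 20%, on those patients remaining in stage D, on the planned difference applying to everyone else, and on an unstated control rate. Under these assumptions 2 to 4 of the 20 points are lost, and the consequence for power runs from modest to large according to the control rate. The 8-point difference under no effect is likewise an illustration; it comes on top of the confounding that the protocol already acknowledges.

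**What to change.** Reconcile sections 3.3, 8 and 10 so that entry and success levels do not overlap. The simplest way is entry at RBHOMS 2–7, which places everyone below stage D at baseline. It is a one-line amendment, at the price of a somewhat smaller pool of mildly affected outpatients.

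If level 8 patients are to stay eligible, or some are already enrolled, define the primary endpoint as moving from below stage D at baseline to stage D. Test it in all participants with baseline RBHOMS 2–7, keep the intention-to-treat principle of section 11 within that set, and use level 8 entrants for the secondary outcomes only. This is not free: the analysed number and power fall as shown in the working, and the protocol should say so. To retain 60 analysable per arm would take 60/(1 − f), that is about 67, 70 or 75 per arm before the dropout allowance. Even without extra recruitment, the subset analysis is no worse in power than leaving level 8 entrants in.

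Either way, section 11 should name the stage D comparison as the quantity tested by the chi-square test, and section 10 should state the control rate behind the 60 per group.
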